## Evaluation

- Primary Endpoint: time to virological treatment failure and /or death and/or AIDS-associated events (clinical treatment failure)

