**Synopsis**

**Title:** A randomized controlled trial to assess the impact of peer support to children and adolescents with HIV receiving antiretroviral therapy (ART) with virological treatment failure as primary endpoint

**Primary Objectives:** To study the impact of peer support to care takers of children with HIV receiving ART vs conventional care on rates and time to virological treatment failure and /or death and/or AIDS-associated events (clinical treatment failure) up to 24 month using a randomized controlled trial (RCT) design comparing enhanced treatment support (ETS) and conventional treatment (CT).

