**Secondary Objectives:**

1. To compare the rate of and time to virological treatment failure (primary endpoint) immunological failure (secondary endpoint) /death/AIDS-associated events (tertiary endpoint) between the intervention and control group
2. To compare the rate of ART adherence between the intervention and control group
3. To compare the rate of acquiring OI’s, drug adverse effect, physical development, drug resistance between the intervention and control group.
4. To asses quality of life in intervention and control group before and after intervention
5. To assess cost effectiveness of peer support comparing to conventional care

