**Indicators for Evaluation:**

The primary endpoint is time to virological treatment failure; the secondary endpoints are time to immunological and clinical treatment failure. In addition adherence will be assessed, risk factors of treatment failure will be evaluated and ART resistance mutations will be assessed. Adverse events including ARV adverse drug reactions, immune reconstruction inflammatory syndrome (IRIS) and OIs development, as well as Death/Mortality will be assessed. Loss of follow-up will be determined after the follow up period for patients who do not attend clinical visits and laboratory monitoring and will be analyzed as death. According to intention to treat patients that are absent one or more follow up visits and then turn up will be included in the analysis. Cost effectiveness will be assessed if there is a significant difference after two years follow up between the intervention and control group using costing analysis.

| No. | Indicator | Method of measurement | Method of assessment |
| --- | --- | --- | --- |
| 1 | Time to Virological treatment failure  (primary endpoint) | Viral load test:  -Baseline at enrollment  -Every 6 months of follow-up period | Cutoff (1): 1000 cps/ml (International)  - If the viral load Is above the cut off in the first assessment after 6 months of ART, it is defined as primary virological treatment failure, if the viral load is first suppressed and then detectable, it is referred as secondary virological treatment failure. |
| 2 | Time to Immunological treatment failure (secondary endpoint) | CD4 count:  - Recent result or baseline at enrollment.  Not part of routine follow up but if indicated due to virologic failure. | *Cutoff : below the level of severe immunodeficiency by age  -Child<11 months: % CD4<25%  -12 month <Child<35 months: %CD4<20%  - 35 months <Child<5 years: %CD4<15%  -Child>5 years: CD4 < 100 cell/mm3  *CD4 count falls to or below cutoff after initial recovery response (1). OR CD4 count falls rapidly below cutoff by age as confirmed by at least 2 consecutive times (2). OR CD4 count falls below more than 50% of the peak level during ARV treatment (3).  Decide %, the time length leading to immunological treatment failure in both group (EST & CT) |

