## Interval Assessments

### Interval history and physical exam

The Procedure of following up both groups EST (every 6 months/24-36 months of follow-u) and CT (as OPC routine procedure according to national guidelines)

- Vital signs and weight
- Physical examination
- Physics development and awareness
- Signs and symptoms of OIs

etc.

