### Interval laboratory test

Patients of 2 groups will be followed for 24 months and monitored every 6 months for viral load. Other laboratory tests schedule as in National guidelines.

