**Peer Support Intervention**

**Follow-up 24 months**

**Analysis**

**Appendix 1 B: Trial Flow Chart for both groups (EST and CT)**

|  |  |  | **24 months follow-up**  **Every 6 months = 6 interval assessment** | | | |
| --- | --- | --- | --- | --- | --- | --- |
| **Event** | **SCR** | **Baseline or enrollment** | **1^st^** | **2^nd^** | **3^rd^** | **4^th^** |
| Informed Consent | x |  |  |  |  |  |
| Inclusion/Exclusion Criteria | x |  |  |  |  |  |
| Medical History | x |  |  |  |  |  |
| Clinical Assessments (vital signs, weight, physical exam) |  | x | x | x | x | x |
| Medication Adherence Assessment (if under ART already) |  | x | x | x | x | x |
| Adverse Event Assessment |  | x | x | x | x | x |
| CBC |  | x | x | x | x | x |
| Liver Enzymes Tests |  | x | x | x | x | x |
| AFB sputum (if available) |  | x | If (indicated) | | | |
| CD4 (if available) |  | x |  |  |  |  |
| Viral load |  | x | x | x | x | x |
| Genotype resistance  (0.5 ml plasma) |  | x | If (indicated) | | | |
| -80 oC Stored plasma  (0.5 ml plasma) |  | x | X | X | x | x |

Volume of Blood sample: 3-4 ml/time, assuming having 1.5 ml of plasma enough for VL, genotypic and storage

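### The primary endpoint is defined in two incompatible ways, as virological failure alone and as a composite with death and AIDS-associated (clinical) events

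*Protocol*

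**What the plan says.** **Virological failure alone is primary** in three places:
- The title in the Synopsis describes a trial "with virological treatment failure as primary endpoint".
- The Secondary Objectives rank "virological treatment failure (primary endpoint) immunological failure (secondary endpoint) /death/AIDS-associated events (tertiary endpoint".
- The Indicators for Evaluation state: "The primary endpoint is time to virological treatment failure; the secondary endpoints are time to immunological and clinical treatment failure". Row 1 of the table there repeats the virological label.

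**A composite is primary** in two places:
- The primary objective in the Synopsis joins virological failure, death and AIDS-associated events, up to 24 months.
- The Evaluation section gives the primary endpoint as "time to virological treatment failure and /or death and/or AIDS-associated events (clinical treatment failure".

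**Death and loss to follow-up.** The Indicators text and row 12 of its table treat loss to follow-up as death. Statistical Considerations counts death and loss as failure in the survival analysis. None of these says which endpoint is meant.

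**Assessment schedule.** Under Interval history and physical exam, the intervention arm is seen every 6 months over 24–36 months "and CT (as OPC routine procedure according to national guidelines". Interval laboratory test says: "Patients of 2 groups will be followed for 24 months and monitored every 6 months for viral load". Appendix 1 B, one chart for both groups, marks clinical assessments at baseline and four follow-up visits, under the header "Every 6 months = 6 interval assessment".

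**The concern.** A confirmatory trial needs one primary endpoint fixed before the data are seen. Here the analyst could report either version as primary and cite the Protocol for it. If the two disagree, the choice can follow the result.

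The versions also differ in how exposed they are to detection bias. Viral load is a laboratory value taken every 6 months in both arms. Clinical failure (row 3 of the indicator table) rests on physical examination, growth and new or recurrent infections. Only the intervention arm has weekly telephone contact and monthly home visits, so supporters may hear of clinical events earlier or more often there. Death is much less exposed to this.

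**Working it through.** **1. The statements side by side**

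| Place in the Protocol | Primary endpoint | Rank of clinical failure / AIDS events |
|---|---|---|
| Synopsis, title | virological | not stated |
| Synopsis, primary objective | composite | primary component |
| Secondary Objectives | virological | tertiary (death/AIDS events) |
| Indicators, text | virological | secondary |
| Indicators, table rows 1 and 3 | virological | tertiary |
| Evaluation | composite | primary component |

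These cannot all hold. If the rule in Statistical Considerations applies to the virological endpoint, a third version appears: virological failure, death or loss.

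**2. Does the sample size settle it?** The inputs are 15% vs 10% treatment failure at 2 years, 80% power, two-sided 5% and 10% loss. The stated result is about 540 in total (260 per group). The usual formula is

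n = [1.96·√(2p̄(1−p̄)) + 0.8416·√(p₁(1−p₁)+p₂(1−p₂))]² / (p₁−p₂)², with p̄ = 0.125.

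This gives (0.9167 + 0.3925)² / 0.0025 = 686 per arm, or 1,372 in total. Dividing by 0.9 gives 763 per arm, or 1,526. The stated 540 is not reproduced, which is a separate defect. It gives no clue to which endpoint was meant.

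**3. Type I error from choosing the better test.** Virological failure (V) is contained in the composite (C). Assume no treatment effect, a virological rate of 12.5% (the mean of 15% and 10%), and other events adding a proportion c independently. The value of c is not in the Protocol. Then p_C = 1 − 0.875(1−c), and the correlation of the two test statistics is ρ = √[p_V(1−p_C) / (p_C(1−p_V))]. The chance that at least one two-sided 5% test is significant, from the bivariate normal, is:

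| c (assumed) | p_C | ρ | Type I error |
|---|---|---|---|
| 1% | 13.4% | 0.96 | 6.3% |
| 2% | 14.3% | 0.93 | 6.7% |
| 5% | 16.9% | 0.84 | 7.5% |
| 10% | 21.3% | 0.73 | 8.2% |

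Independent tests would give 1 − 0.95² = 9.75%, but nested endpoints are not independent.

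**4. Power.** Power = Φ{[(p₁−p₂)√n − 1.96√(2p̄(1−p̄))] / √(p₁(1−p₁)+p₂(1−p₂))}, with n = 270 per arm (540/2). For 15% vs 10% this is Φ{(0.8216 − 0.9167)/0.4664} = 42%. Add 5% other events (assumed):
- With no effect on them: 1 − 0.85×0.95 = 19.3% vs 1 − 0.90×0.95 = 14.5%; power 31%.
- Cut by one third, as assumed for virological failure: 19.3% vs 1 − 0.90×0.967 = 13.0%; power 51%.

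At 243 per arm (270 × 0.9) the three figures are 38%, 29% and about 47%. The direction depends on the assumption.

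**5. Loss counted as failure.** If the planned 10% loss is equal in both arms, independent of outcome and counted as failure, the rates become 1 − 0.85×0.90 = 23.5% vs 1 − 0.90×0.90 = 19.0%. Power at 270 per arm is then 25%. This rule matters as much as the choice between the two versions.

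**6. Schedule.** 24 months / 6 months = 4 assessments, which matches the four columns in Appendix 1 B. Six assessments would need 6 × 6 = 36 months, the upper end of the range under Interval history and physical exam.

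**The case against.** The best defence is that the practical gap is smaller than it looks. Statistical Considerations already counts death and loss as failure, so death may enter under either label, leaving mainly the clinical and AIDS events. That is a fair reading, but it still leaves two endpoints, and the Protocol does not say that the rule applies to the primary one.

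Two stronger readings are tempting and should not be drawn:
- **That the arms are examined on different schedules, or that the intervention arm is followed longer.** Only Interval history and physical exam separates the arms, and it gives no interval for the control arm. The primary objective, Study Duration and Interval laboratory test all point to 24 months. Appendix 1 B gives both groups the same visits, and control adherence support is itself 6-monthly. This is a conflict in the text, not evidence of unequal follow-up. The count of six in Appendix 1 B may be a header slip, since the chart has six columns including screening and baseline.
- **That the composite necessarily costs power, or that type I error approaches 10%.** The power loss reverses if the intervention also reduces clinical events, and nesting keeps the error well below 10%.

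It can also be said that preferring virological failure is a reviewer's choice. The documents support both versions; what they require is that one be fixed.

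**Conclusion.** The contradiction is established by the current text and does not depend on any calculation. It must be resolved because it allows two primary results from one dataset. If the better result were chosen, type I error would be roughly 6–8%. That range rests on assumed independent added events of 1–10%, a 12.5% virological rate in both arms, and a comparison of proportions at 24 months as a stand-in for the time-to-event test. No direction can be given for power. The schedule conflict is secondary: it needs reconciling, but unequal assessment in practice is not shown.

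**What to change.** 1. State one primary endpoint, in the same words and with a 24-month cut-off, in the Synopsis, Secondary Objectives, Indicators for Evaluation and Evaluation sections. Virological failure has the stronger case: it is in the title, the Secondary Objectives and the Indicators, is measured 6-monthly in both arms, and is less exposed to the extra contacts in the intervention arm.
2. Make the other version a named secondary endpoint and rank each component once.
3. Amend the Indicators text, row 12 of its table and Statistical Considerations to say how death and loss to follow-up are handled for the chosen endpoint. Without this, a purely virological definition would still conflict with those places.
4. Say which endpoint the 15% and 10% planning rates refer to.
5. Reconcile Interval history and physical exam with Interval laboratory test and Appendix 1 B, so that endpoint assessments follow one schedule in both arms, and correct the count of six or the period.

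No new data are needed, but this is more than an edit. Enrolment was planned for the second quarter of 2019 and the questionnaire asks about COVID-19, so this text may postdate the start of enrolment. The monitoring board reviews annually and may act on the primary outcome. The decision should therefore be documented, dated and taken by people blind to outcome data by arm, with ethics approval of the amendment as the Protocol requires.

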## Statistical Considerations

- The statistical analysis mainly consists in the comparison between the two groups ETS and CT with respect to the defined primary and secondary endpoints in relation to the semi-quantitative assessment of adherence (by questionnaire, pill counts, and pharmacy records).
- Standard statistical methods will be used. Hazard/Survival analysis will be conducted including death/loss of follow up as “failure” in the analysis. Intention to treat will be used for analysis.
- Regression models with outcome as the dependent variable and a group indicator together with patient characteristics as independent variables will be the main approach.
- For binary outcomes, logistic regression will be used.
- Attention has to be paid to the particular, often skewed, distributions of variables like viral load. Transformations or the use of non-parametric approaches are likely to be necessary if such measures are not dichotomized and used in linear regression.
- The correlation between drug resistance and adherence will be statistically analysed in order to study whether the basic mechanisms of selective drug pressure result in a concave or bell-shaped resistance – adherence relationship (Friedland and Williams, 1999), for these drugs during ETS or CT in a low-income setting.
- The odds ratios of having or not baseline drug resistance mutations as detected by population and deep (single allele PCR) sequencing on drug resistance development and clinical outcomes during treatment independent of treatment adherence will be evaluated.
- Stratified analysis will be conducted comparing the outcomes among the treatment groups.

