**Sample size:**

WHO sample formula for the intervention study, comparing to 2 proportions

We assume the possibility of treatment failure of 15% in the control arm and 10% in the intervention arm after 2 years of follow-up. With 80% power and a test at the two-sided 5% significance level, 10% losses of follow-up, approximately 540 patients are required **(260 per group)** into the trial.

**Enrollment:** All patients aged 10-18 years meeting the inclusion criteria are eligible at the study sites will be enrolled.

**Randomization:** The patients are randomized in the intervention or control group the first time of the intervention. E.g. all patients that attend the examination at a specific weekday will be included in intervention group other week day will be the control group. The peer group meetings will then be organized according to the day of examination where each group contain about 15 patients. Patients can/will not know which day is which until they come to avoid bias. Written consent will be done.

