| 3 | Clinical treatment failure (tertiary endpoint) | - Physical exam  - WHO scale in infant development (weight, height, physically active) | - Lack of or decline growth rate in children who initially respond to treatment (1).  - Loss of neurodevelopmental milestone or development of encephalopathy (2).  - Occurrence of new OIs or malignancies or recurrence of bacterial or fungal infections that refractory to treatment (3).  Decide %, the time length leading to clinical treatment failure in both group (EST & CT) |
| 4 | Adherence assessment | - Interview  - Questionnaire  - Pill count  - Pharmacy record | * Cut-off: (Good > 95%, Poor <95%)  - Good adherence: > 95% doses taken on time  - Poor adherence: < 95% doses taken OR > 95% doses taken but not on time.  * Other factors related:  - On time at every check-up visit  - Same caretaker at every check-up visit  - The current belief of caretaker to ART  - The current collaboration of child to ART  Decide % adherence in both group (EST & CT) |
| 5 | Risk factors of treatment failure | - Questionnaire  - Counseling | - Decide the pattern of risk factors of both groups and compare. |
| 6 | ART mutation assessment | - Genotyping (sequencing or real-time PCR for specific allele) | * ART mutation assessment for patients that have detectable viral load above 1000 copies/ml  * Baseline resistance will be assessed in a subsample of the cohort.  * Compare to Stanford HIV mutations database regarding to the regimens that patients were treated.  Decide pattern of mutation, % in both group (EST & CT) |
| 7 | ARV adverse effects | - Physical exam  - Lab test (enzyme) | Decide % of children having ARV adverse effects from both group (EST and CT) |
| 8 | IRIS | - Physical exam | Decide % of children having IRIS from both group (EST and CT) |
| 9 | OIs development | - Physical exam | Decide % of children having OIs development from both group (EST and CT) |
| 10 | Death/Mortality | - Regardless death causes | Decide % of children death from both group (EST and CT) |
| 11 | Development of AIDS events | - Physical exam | Decide % of children with development of AIDS events from both group (EST and CT) |
| 12 | Loss of follow-up  = Death (in analysis) | - Not able to manage within 6 months. | Assume as death/mortality in analysis.  These patients will be drawn out of study, If they come back to OPC, they will receive support as conventional procedure. |

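### Virological failure is seen only at six-monthly tests, and the planned standard survival analysis has no provision for this; if CT visits run later than ETS visits, detection-date analysis can pull the hazard ratio toward or past 1

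*Protocol*

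**What the plan says.** The protocol's Indicators for Evaluation section makes the primary endpoint a time to virological failure at a 1000 copies/ml cut-off. The Evaluation section adds death and AIDS-associated events. Viral load is taken at baseline and then "Every 6 months of follow-up period". The section Interval laboratory test applies the same schedule to both arms: "Patients of 2 groups will be followed for 24 months and monitored every 6 months for viral load". Appendix 1B shows four follow-up assessments.

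On method, Statistical Considerations says "Standard statistical methods will be used. Hazard/Survival analysis will be conducted", with death and loss to follow-up counted as failure. It gives no rule for the event date or the censoring date of a viral-load failure, and names no method for interval-censored or discrete times.

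On attendance, children with gaps are kept: "patients that are absent one or more follow up visits and then turn up will be included in the analysis". Loss is declared only after six months. The adherence indicator lists "On time at every check-up visit" among its related factors, for both arms. According to the peer-supporter assignment table and the Peer Support Intervention section, only ETS families receive weekly calls, monthly home visits and monthly group meetings, and the meetings are tied to clinic days.

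**The concern.** A viral load above the cut-off at one visit, after one below it at the previous visit, places the failure somewhere in an interval of about six months. Ordinary survival software needs a single date. The usual choice is the date of the positive test, with event-free children censored at the date of their last negative test. Failure time is then partly visit time.

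This does no harm when both arms attend equally punctually. It matters when they do not, mainly at month 24. If CT children come later, most event-free ETS children have already been censored when the CT failures at that visit are dated. Those failures have few ETS children in their risk sets and hardly count in the comparison. ETS failures at the same visit are dated earlier, while most CT children are still at risk, and count in full.

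If peer contact improves punctuality, the distortion runs against ETS: a real benefit is diluted, and an ineffective programme can look harmful. The opposite attendance pattern reverses the direction.

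**Working it through.** **Inputs from the protocol.** The Sample size section assumes "treatment failure of 15% in the control arm and 10% in the intervention arm after 2 years of follow-up". Its other settings are a two-sided test at 5%, power of 80% and an allowance of 10% for loss. It arrives at a total of 540 but also at 260 in each group (2 × 260 = 520, so the two sizes do not agree; 260 to 270 per arm were used). Tests fall at 6, 12, 18 and 24 months.

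**Assumptions.** Constant hazards, which give a true hazard ratio of ln 0.90 / ln 0.85 = 0.648. Each visit is delayed by an exponential time. The protocol gives no delays; the means used are CT v ETS 0.5 v 0.25 and 1 v 0.25 month.

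**Step 1: the plan's own figure.** n per arm = [1.96√(2 × 0.125 × 0.875) + 0.8416√(0.15 × 0.85 + 0.10 × 0.90)]² / 0.05² = 686. That is 1372 in total, or 1372 / 0.9 ≈ 1525 after 10% loss. The stated 540 does not reproduce. Power at 260 per arm is Φ[(0.05√260 − 0.9167) / 0.4664] = Φ(−0.237) = 40.6%; at 270 it is 41.9%. So about 41% is the starting point before any question of visit timing.

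**Step 2: hand check of the mechanism, no true effect, 260 per arm.**
- Failures per arm: 260 × 0.15 = 39. Found at the month-24 visit: 260 × (0.85^0.75 − 0.85) = 260 × 0.0352 = 9.2.
- Delays of 1 v 0.25 month: averaged over the delay distribution, the ETS share of the risk set is 0.164 at a CT failure and 0.343 at an ETS failure (0.5 each with equal delays). Expected ETS failures at month 24 are 9.2 × (0.164 + 0.343) = 4.6, against 9.2 observed. The excess is 4.5.
- Log-rank variance: about 2 × 29.8 / 4 = 14.9 from the first three visits plus 2.9 from the fourth, 17.9 in all. One-step hazard ratio: exp(4.5 / 17.9) ≈ 1.29. Shift in z: 4.5 / √17.9 = 1.07, so about 19% false positives.
- Delays of 0.5 v 0.25 month: the shares are 0.307 and 0.386, the excess 2.8 and the variance 18.8. The hazard ratio is exp(2.8 / 18.8) = 1.16, with about 10% false positives.

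The excess comes from the month-24 visit.

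**Step 3: simulation, actual dates, event-free children censored at their own last visit** (Monte Carlo error about 1 to 2 percentage points).

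| Endpoint | Quantity | Equal punctuality | 0.5 v 0.25 to 1 v 0.25 month |
|---|---|---|---|
| Virological failure only | Null hazard ratio | 1.00 | 1.16 to 1.26 |
| | False positives | about 5% | 10% to 18% |
| | Hazard ratio, 15% v 10% | 0.65 | 0.74 to 0.81 |
| | Power | about 41% | about 14% to 21% |
| With 10% loss as failure, assumed equal by arm | Null hazard ratio | – | 1.07 to 1.12 |
| | False positives | – | 7% to 9% |
| | Power | about 26% | about 10% to 14% |

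**Step 4: other date rules under unequal delays, virological failure only.** With a common late censoring date, a cut at 24 months, or nominal visit numbers, the hazard ratio for 15% v 10% stays at 0.61 to 0.65 and power at 33% to 54%.

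**Step 5: interval-censored model, 260 per arm.** For 15% v 10% the hazard ratio is 0.64 to 0.65 and power 40% to 42% across the delay patterns, with 4.7% to 6.0% false positives under the null.

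**The case against.** The strongest reply is that the protocol fixes none of the rules on which the distortion depends. It does not say that failures are dated at detection or where event-free children are censored. Interval-censored and discrete-time models are themselves survival analysis. Such rules commonly sit in an SAP, which is not shown, so their absence is not an error. This stands. The point is that the one method named is the standard one, and a more robust choice is available.

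A reader might infer that punctual attendance is a declared target of ETS. The text does not support that. On-time attendance is a measured factor related to adherence in both arms. The automatic reminders concern medicine, and the calls confirm home visits and ask after the patient. An effect on clinic punctuality is an inference from the extra contact and the clinic-day meetings.

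A reader might also infer that the primary hazard ratio is biased as planned, or that power falls from 41% to 14%. Neither follows. Three conditions must hold together: unequal delay, actual dates and own-last-visit censoring. An ordinary log-rank test on nominal visits, or with times cut at 24 months, avoids the loss. The 14% rests on assumed delays and leaves out the plan's loss-as-failure rule, which lowers the starting power and shrinks the distortion.

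**Conclusion.** The point holds as a conditional weakness and an inexpensive improvement, not as a demonstrated bias. Six-monthly testing alone does no material harm. Under the common dating default, a difference in mean delay of a quarter of a month, about one week, is enough to raise false positives to about 10% for virological failure alone, or about 7% with loss counted as failure. At 1 v 0.25 month the figures are about 18% and 9%, nearly all against ETS in the virological-only runs.

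These sizes rest on constant hazards, exponential delays that the protocol does not give, and loss assumed equal in both arms. The starting power of about 41% is a separate and larger sample-size problem. Correcting the analysis removes the distortion but does not bring power near 80%.

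**What to change.** In Statistical Considerations (or the SAP), specify for the virological endpoint an interval-censored proportional-hazards model, bounded by the last viral load below the cut-off and the first above it. A discrete-time or nominal-visit model on visits 1 to 4 is an acceptable alternative. Count the month-24 viral load whenever it is taken, and let a missed visit widen the interval. If death and AIDS-associated events stay in the endpoint, enter them at their own dates. Keep detection-date Cox as a sensitivity analysis, and settle the choice before outcomes are compared by arm.

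The cost is one paragraph and available software; no extra visits, data or patients are needed. The downside is a less familiar model. The nominal-visit version also keeps a slight bias when delays are large: its null hazard ratio was about 0.97 to 0.98 at 1 v 0.25 month and about 0.93 at 2 v 0.5 months. The interval-censored version stayed at about 1.00 in both.

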## Peer Support Intervention “Enhanced Treatment Support (ETC)”

1. Caretakers of children and adolescents with HIV on ART will be supported to achieve better adherence through peer support groups and phone follow-up, with an option for home visits or to return to support groups later if necessary. The activities will be organized by peer supporters, HIV-infected young adults selected by peers who will undergo a series of training, including medication adherence and counselling skills.

The support will include

1. Peer group support:

- Home visit
- Telephone support
- Focus group discussion

1. More support during medical visit
2. Peer group meetings with about 15 children and adolescents and their supporters arranged according to age groups of children and adolescents 10 – 12 years , 16 years as well as according to location, e.g. one group per age group per district. Each peer group meeting will be arranged by two peer supporters, one that takes care of the caretakers and the other the children. Each peer group meeting should have a generic part in relation to adherence where each caretaker can bring up problems and discuss them with the supporter and other group members. At each meeting some new information will be provided, either from the supporter or by some invited person arranged by the project, according to a training program.
3. The supporters will also have at least one telephone contact with the caretakes per week, if needed more, to assess the condition of the child/adolescent. To those who cannot make a particular support group session phone calls or home visits (if consent is given) are made. Follow up phone calls will be made to those whom the case manager identifies to need more support.
4. The meeting will be arranged in relation to the treatment day, e.g. at ND1 on Mondays and Wednesdays, when the patients are available at the clinic.
5. The peer-supporters will be trained by the research team and given training material to share with their Peer support groups. The training will include: Basic HIV knowledge review, Nutrition and HIV, Opportunistic Infections, Mental health, Antiretroviral Therapy and Adherence, Medication Adherence Support, Role of the peer-supporters, Setting boundaries and working as part of multidisciplinary team, Disclosure, Outreach overview, Confidentiality, Counseling skills, Study forms (CRF) and reports

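### Enhanced treatment support is delivered in peer groups of about 15 under shared supporters, but neither the sample size nor the stated main regression allows for correlation within groups

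*Protocol*

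**What the plan says.** The Peer Support Intervention section describes "Peer group meetings with about 15 children and adolescents and their supporters arranged according to age groups", formed by age band and by location, and adds: "Each peer group meeting will be arranged by two peer supporters". The assignments table for peer supporters sets group meetings once a month in ETS and none in CT. ETS also includes weekly calls, home visits and reminders.

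Under Sample size, the method is given as "WHO sample formula for the intervention study, comparing to 2 proportions". The inputs follow: "We assume the possibility of treatment failure of 15% in the control arm and 10% in the intervention arm after 2 years of follow-up". The operating characteristics are also stated: "With 80% power and a test at the two-sided 5% significance level". A 10% allowance for loss to follow-up leads to about 540 children, with 260 per group. No design effect, ICC or number of peer groups appears.

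Statistical Considerations gives the analysis in outline: standard methods, survival analysis, logistic regression for binary outcomes, and "Regression models with outcome as the dependent variable and a group indicator together with patient characteristics as independent variables will be the main approach". It names no peer-group or supporter term, frailty, random effect or robust variance.

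Randomisation is described in two ways. Study Designs has 1:1 randomisation stratified by centre and ART status. The Randomization paragraph next to the sample size gives, as its example, allocating all children seen on one weekday to the intervention and those seen on another to control, with peer groups organised by examination day.

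**The concern.** The supporter and the group are much of what ETS delivers. If some supporters or groups work better than others, that variation is shared by about 15 children at a time, and in one arm only. An analysis that treats every ETS child as an independent observation then counts more information than the arm contains. The standard error of the arm difference would be too small and the confidence interval too narrow. A few strong or weak supporters could move the result more than the reported uncertainty suggests. The stated power would be too high for the same reason. Stratifying by centre and ART status does not deal with correlation inside a peer group.

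**Working it through.** **Inputs from the Protocol.** Failure 15% (CT) and 10% (ETS) at two years; two-sided 5%; 80% power; 10% loss; about 540 in total; peer groups of about 15. Per-arm size is taken as 540/2 = 270. The Protocol also says 260 per group, which sums to 520.

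**Assumed.** ICC of 0.01, 0.02 or 0.05, because the Protocol gives none.

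**Step 1: the plan's own figure under independence.** The usual pooled two-proportion formula gives 686 per arm, or 1372 in total; with 10% loss, 686/0.9 = 763 per arm, or 1526. The unpooled formula gives (0.15×0.85 + 0.10×0.90) × (1.960 + 0.842)² / 0.05² = 0.2175 × 7.849 / 0.0025 = 683 per arm. The stated 540 is not reproduced. A one-sided 5% pooled calculation without loss gives 540 per arm, but the Protocol states a two-sided test and 540 in total.

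Power with 270 per arm: standard error = √(0.2175/270) = 0.0284; 0.05/0.0284 − 1.960 = −0.198; power = Φ(−0.198) = 42%. With 260 per arm it is 41%.

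**Step 2: clustering in ETS only.** This is the case if randomisation is individual. The formulas are:

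- Design effect: DE = 1 + (15 − 1) × ICC.
- Variance ratio of the arm difference at the planned rates: (0.1275 + 0.09 × DE)/0.2175.
- Variance ratio with equal arm variances: (1 + DE)/2.
- True level of a nominal 5% test that ignores clustering: 2 × [1 − Φ(1.96/√((1 + DE)/2))].
- Power with 270 per arm: Φ(0.05/√((0.1275 + 0.09 × DE)/270) − 1.96).
- Children per arm for 80% power before loss: (0.1275 + 0.09 × DE) × 7.849/0.0025.

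| Assumed ICC | DE | 270 ETS children are worth | Variance rise, 15% vs 10% | Variance rise, equal variances | True level | Power, 270 per arm | Per arm for 80% (after 10% loss) |
|---|---|---|---|---|---|---|---|
| 0 | 1.00 | 270 | 0% | 0% | 5.0% | 42% | 683 (759) |
| 0.01 | 1.14 | 237 | 6% | 7% | 5.8% | 40% | 723 (804) |
| 0.02 | 1.28 | 211 | 12% | 14% | 6.6% | 38% | 762 (847) |
| 0.05 | 1.70 | 159 | 29% | 35% | 9.2% | 34% | 881 (979) |

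Worked line, ICC 0.05: DE = 1 + 14 × 0.05 = 1.70. Variance ratio = (0.1275 + 0.153)/0.2175 = 1.29. Equal-variance ratio = 2.70/2 = 1.35, square root 1.162; 1.96/1.162 = 1.687, which gives 9.2%.

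**Step 3: clustering in both arms.** This applies if whole weekdays are allocated. Keeping 15 per cluster for illustration, the standard error is too small by √DE. The true level becomes 6.6%, 8.3% or 13.3% at the same ICCs, and power with 270 per arm falls to 38%, 34% or 27%. Larger clinic-day clusters at the same ICC would make this worse.

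**The case against.** The strongest reply is that Statistical Considerations is only an outline. It does not exclude a frailty term or robust variance, and such detail commonly sits in a statistical analysis plan, which is not available here. That stands for the model. It does not help the sample size, which the Protocol fixes without a design effect. A later plan also cannot use a group identifier that was never collected. The questionnaire sections in the Protocol show no such field, although the full online case report form is not shown.

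A reader might infer more than the Protocol supports, in three ways:

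- **That the standard errors and p-values are certainly too small.** This needs a positive ICC, and the Protocol gives none. At 0.01 the effect is minor.
- **That sharing an age band and a district is itself a source of the problem.** Control children have ages and districts too. Under individual randomisation these similarities occur in both arms and do not by themselves inflate the variance of the difference. Only correlation produced by the supporter, the group or the clinic day counts.
- **That the false-positive rate must exceed 5%.** If peer support changes nothing for any child, supporters induce no correlation and an individually randomised test keeps its level. The levels above apply when group effects differ but average to zero.

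Parts of ETS are also delivered child by child, which may keep the ICC low, although the supporters may be shared there too.

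**Conclusion.** The point holds in conditional form. The Protocol documents group delivery under shared supporters and makes no allowance for it in the sample size or the stated main model. If the resulting ICC is positive, the ETS variance is understated. Over the assumed ICC range the consequence runs from minor to material. The size rests on groups of 15, on 270 per arm and on clustering in ETS only.

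Whether ETS-only clustering is the right picture depends on which description of randomisation is followed. Under weekday allocation the clinic day is a possible cluster in both arms, and treating control children as independent would leave that unhandled.

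The larger power deficit is separate. Even under independence the stated inputs do not give 80% at this size. Clustering lowers a power of about 42% further; it does not explain the gap.

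**What to change.** 1. Record peer-group, peer-supporter and clinic-day identifiers in the case report form, with group and supporter fields left empty for control children.
2. Reconcile Study Designs with the Randomization paragraph, and state the unit of allocation.
3. State in Statistical Considerations that the primary model accounts for clustering. If randomisation is individual, use a partially nested model: a frailty or random intercept per ETS peer group with control children as singletons, or cluster-robust standard errors with a small-sample correction. With 270/15 there would be only about 18 groups, a number that the Protocol does not itself give. If weekdays are allocated, take clinic day as the cluster in both arms.
4. Restate the power over an assumed ICC range with its source, starting from the recomputed base under independence and not from the stated 80%.

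The cost is a few extra data fields, a paragraph of model wording, a somewhat wider confidence interval and a less favourable stated power.
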